### Assessments and outcomes

The main hypothesis of the study is that the “blended ALMAMAR” app can be successfully implemented in inpatient psychiatric-psychotherapeutic care of refugees, and that it is accepted and used by therapists and patients.

The *primary endpoint* will be the use of the “blended ALMAMAR” app during inpatient stay, measured by:

recruitment rate (proportion of eligible patients who signed a consent form to participate);app usage rate (proportion of recruited patients who use the app at least once);average number of modules completed in the app;average duration and frequency of use of the app.

*Secondary endpoints* are clinical assessments, as well as acceptability and usability of the intervention. These will be assessed using questionnaire data from patients and therapists at each of the three time points (baseline assessment at study entry t0, post assessment at discharge t1, and follow-up six months after discharge t2; see Table 2 for an overview of all assessments).

**Table 2 Tab2:** Overview of the planned assessments

	Instrument	Who fills in?	Timepoint of measurement			Estimated duration (minutes)
No.			T0: Baseline (Admission)	T1: Post (Discharge)	T2: Follow-up (six months after discharge)	
1	Sociodemographic data	Patient	x			10
2	User rating of the app (CSQ-8) [30]	Patient		x	x	5
3	Post Migration Living Difficulties Checklist (PMLD) [26]	Patient	x			10
4	Expectation of therapy	Patient	x			5
5	EQ-5D-5 L (Health-related quality of life) [27]	Patient	x	x	x	5
6	*Health care utilization [selected questions from FIMA* [28] *and FIMPsy* [29]:					
	Number and specialisation of outpatient physician contacts in the last six months before inpatient admission (or baseline) and in the six months after discharge	Patient	x		x	3
	Number of inpatient stays and treatment days in the last six months before inpatient admission (or baseline) and in the six months after discharge	Patient	x		x	3
	Diagnoses, medications	Patient	x		x	3
	Number of visits to emergency departments in the last six months before hospitalization (or baseline) and in the six months after discharge	Patient	x		x	1
	Current employment [yes/no]	Patient	x		x	3
7	Main diagnosis of mental disorder and secondary diagnosis(es)	Therapist	x	x		1
8	Number of inpatient psychiatric treatment days and stays in the last six and twelve months, respectively	Therapist	x	x	x	3
9	Symptom severity (CGI) [31] and functional ability (GAF) [32]	Therapist	x	x		5
10	Regular insurance status [yes/no]	Therapist	x			1
11	Assessment of therapy success [rating 1–5]	Therapist		x		1

At baseline, patients fill out questionnaires on post-migration stressors (27-items post-migration living difficulties checklist (PMLD); [26]), expectations for the current therapy (3 items; self-developed questionnaire), and health-related quality of life (EQ-5D-5 L; [27]). Additionally, we assess costs of health care utilization by selected questions from the FIMA [28] and FIMPsy [29] questionnaires by asking about the number of physician contacts and inpatient stays within the last six months before admission/baseline and about the duration of these inpatient stays, past diagnoses, medication and current employment status. Asylum-related factors (e.g. length of stay, asylum status) are assessed at baseline. At discharge, patients fill in a user rating of the app (adapted version of the CSQ-8; [30]) as well as the health-related quality of life (EQ-5D-5 L; [27]).

Therapists will indicate the current main diagnosis of mental disorders as well as secondary diagnoses. In addition, they will perform clinical ratings of symptom severity (CGI; [31]) and functional ability (GAF; [32]) at each assessment. They will indicate the number of inpatient psychiatric treatment days (at post-assessment) and perform a rating of overall therapy success at discharge (rating 1–5). In case of dropout, therapists document reasons. In a separate assessment, therapists will be asked about their attitudes/expectations and experiences with digital interventions before working with the app (pre-assessment) and after approximately 12–24 months of experience with the app (post-assessment). For this assessment, we created short questionnaires that are given to all therapists after an initial app training session.

### Implementation process

We use the RE-AIM model (reach, efficacy, adoption, implementation, maintenance) as a theoretical framework for the implementation process. This model was originally designed for evaluating interventions to improve general health [33]. It was later adapted for evaluating informatics-based applications in clinical settings [34], and has already been successfully applied [35]. Bakken and co-authors define five dimensions: (1) *Reach* describes the absolute number and proportion of people receiving the intervention and its representativeness of the population; (2) *Efficacy* measures the degree of impact of the intervention in terms of quality of care (for processes and outcomes) and observes unanticipated positive or negative effects of the intervention; (3) *Adoption* refers to the absolute number and proportion of individuals who forgave the intervention and its representativeness of the population; (4) *Implementation* describes, at the setting level, the adherence to the intervention by those who prescribe the intervention, i.e., the consistency of administering the intervention as scheduled, as well as associated time and cost; additionally, at the individual level, the behavior of patients in terms of using the intervention strategies; (5) *Maintenance* includes, at the setting level, the degree to which the intervention is adopted in routine care and, at the individual level, the long-term effects of a program on specific outcomes at six or more months after the last intervention contact. When planning the study, these dimensions of the theoretical model were taken into account. An evaluation of the implementation process according to the dimensions is planned at the end of the project.

### Sample size

This is an implementation study investigating the feasibility and perceived benefits of a nonmedication intervention under routine clinical conditions. The focus is on feasibility and acceptability of the implementation of an app in routine mental health care (blended care) for refugees, not on clinical effectiveness. Across all eight recruitment centers (LVR-clinics), we aim to recruit 100 patients for this study and assume a dropout rate of 20%.

### Ethical aspects

The study protocol as an implementation study and its amendments were approved by the responsible ethics committee (Medical Association of North Rhine [Ärztekammer Nordrhein]; Germany; EK2021113 on July 21, 2021; amendments 6000251823 and 6000255968).

### Data management and data access

All data protection regulations of the German Federal and State Data Protection Acts as well as the General Data Protection Regulation (Datenschutzgrundverordnung, DSGVO) are taken into account within the framework of a data protection concept. A data safety plan was approved by the ethics committee. The data protection requirements have also been agreed upon by the Rhineland State Council (LVR) data protection officer. All data will be directly collected within the “blended ALMAMAR” app. The LVR-Institute for Research and Education (study coordination center) is responsible for quality control and data management. When exporting data from the app to external partners, no personally identifying data (usernames or contact data) are exported. Instead, each data set receives a randomly generated ID and is thus pseudonymized. Anonymous data export (excluding personal data) is currently only planned for partners within the I-REACH consortium and the ancillary project PrevDrop.

### Confidentiality

Patients and therapists will register in the “blended ALMAMAR” app with their E-mail address and/or phone number (for patients optionally, necessary for password reset). All data are stored on a secure platform, and no personal data will be exported from the app. After the trial, data will be stored for ten years. Patients will receive extensive information on data assessment, transfer, storage and access policy within the informed consent procedure.

### Statistical methods for primary and secondary outcomes

Descriptive statistics will be performed for all quantitative variables at t0, t1 and t2. For all categorical variables, numerical and frequency data will be calculated. The main outcome variables (recruitment rate, app usage rate, average number of modules completed in the app, average duration and frequency of use of the app) are descriptive data that can be analysed by recruitment documentation of the clinics as well as log-in data from the app. Regarding secondary outcome variables, we will perform pre-post analyses regarding CGI and GAF as well as health-related quality of life using Wilcoxon test. Intention-to-treat (ITT) and per protocol analysis will be conducted to avoid selective reporting and biases in the analyses. Missing values will be imputed by the appropriate statistical methods depending on the type of missing. FIMA und FIMPsy will be used to measure healthcare utilization which will be multiplied with unit costs to calculate costs. Using these costs, a budget impact analysis will be conducted to analyse the cost impact of introducing “blended ALMAMAR” into routine care.

Subgroup analyses will be performed (e.g. regarding diagnoses and provider location), and predictors and mediators (e.g. PMLD or health-related quality of life scores) will be included as covariates. SPSS software will be used for data analyses and two-sided p-values of p < .05 will be accepted as statistically significant.

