### Recruitment, participant timeline and informed consent

The recruitment phase started in June 2022 and is planned for 31 months (until December 2024). Physicians and psychologists who work as therapists in the wards and day-clinics of the eight LVR hospitals can participate in the study as treatment providers for the “blended ALMAMAR” app (“therapists”). To familiarize therapists with the app “blended ALMAMAR”, a training course for therapists (two hours) was developed. Having participated successfully in this course, therapists obtain access to the app by an individual account. Therapists recruit patients during inpatient stay (see Fig. 1). Patients can be recruited shortly after admission or at some later point during their inpatient stay. After checking the inclusion and exclusion criteria, therapists hand out study information to suitable participants. A demo version of the “blended ALMAMAR” app can be shown for illustration if needed. Written informed consent sheets are available in Arabic, Farsi and German and interpreters can be consulted. Within the informed consent process, patients will be asked whether they agree to be contacted in case of dropout for participation in an ancillary study of the I-REACH consortium which examines reasons for dropout (“Prediction and prevention of dropout in research, diagnostics, and treatment with refugees”; PrevDrop). In case of consent, a separate informed consent is obtained by the participant for their participation in a qualitative interview. After written informed consent has been obtained, therapists give patients access to the “blended ALMAMAR” app to use it in addition to routine care (i.e., a setting blended of smartphone and personal contacts). All participants of the study fill out standardized questionnaires in Arabic or Farsi at study inclusion (t0: baseline assessment), upon discharge from inpatient treatment (t1: post assessment), and six months after discharge (t2: follow-up assessment). There is no predefined length of participation in the study since the duration of inpatient stay may vary largely between patients. At t0 and t1, questionnaires are delivered via the app. Follow-up assessments (t2) are conducted by telephone or via video call by the therapist (if necessary, with the help of an interpreter). In order to ascertain a high call back rate, therapists note the contact details of patients at discharge and can already fix a date for the planned interview.

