### Adjustments of the study design during the course of the project

Some important modifications became necessary in the course of the project:

(1) Initially, when the project was conceptualized in 2017, five of the nine LVR-clinics decided to engage in the blended-care implementation study. As the number of refugees decreased in the following years, we recruited three more clinics. (2) The development of the App (subproject 2 of the I-REACH consortium) was delayed due to the COVID-19 pandemic. Consequently, the implementation study (subproject 4) was delayed. Recruitment of patients started in June 2022 with a delay of 16 months compared to the original plan. (3) Approximately six months after recruitment started, we decided to expand the inclusion criteria by including substance use disorders as an additional diagnostic group. (4) Initially, we had planned a cluster-randomisation with control group design in order to assess potential advantages of the blended care approach compared to treatment as usual (TAU). According to the original study design, half of the recruitment centers should offer TAU and recruit control patients. However, recruitment of a control group proved to be unfeasible in this trial: After six months of futile recruitment efforts, we decided to forgo the control group and focus on the main goal of the planned study, which had been the study of the implementation. Thereafter, the four control group centers were converted into intervention centers. The funding partner, ethics committee and Data Safety Monitoring Board (DSMB) approved this revision of the study concept.

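### The utilisation look-back may end at admission or at baseline, so index-stay days can enter the before-costs but never the after-costs, and without a control group these costs give no comparable without-app scenario

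*Protocol article*

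**What the plan says.** **Cost source.** Under Statistical methods for primary and secondary outcomes: "FIMA und FIMPsy will be used to measure healthcare utilization which will be multiplied with unit costs to calculate costs". The next sentence begins "Using these costs, a budget impact analysis will be conducted to analyse the cost impact of introducing" and goes on to name the app and routine care.

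**Windows.** Table 2, row 6 (Assessments and outcomes) asks patients for: "Number of inpatient stays and treatment days in the last six months before inpatient admission (or baseline) and in the six months after discharge". Outpatient contacts and emergency visits in the same row carry the same bracketed alternative. The text below the table also treats the two dates as one: "inpatient stays within the last six months before admission/baseline".

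**Timing of baseline.** The recruitment section defines t0 as study inclusion and adds: "Patients can be recruited shortly after admission or at some later point during their inpatient stay". It sets no upper limit on the delay and notes that length of stay varies widely. The column heading of Table 2, however, equates t0 with admission.

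**Comparator.** Under Adjustments of the study design: "After six months of futile recruitment efforts, we decided to forgo the control group". Then: "Thereafter, the four control group centers were converted into intervention centers".

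**Second source.** In Table 2, row 8, therapists report inpatient psychiatric treatment days and stays over the preceding six and twelve months at t0, t1 and t2.

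**The concern.** There are two separate problems.

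The first is the window. Admission and baseline are offered as if they were the same date, but the recruitment section allows them to differ by any part of the stay. If the look-back ends at a later baseline, the days already spent in the index stay count as prior utilisation, and so does the index admission. No matching days can appear after discharge. For inpatient days, the costliest item, the error runs one way: towards an apparent reduction.

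The second is the comparison. A cost impact of introducing something needs costs with it and costs without it. Once the control centres were converted, every patient supplying these data is an app patient. The only contrast within the named data is the period before an admission against the period after discharge. Patients selected because they were admitted will tend to use less care later whatever the app does, and all of them receive full inpatient treatment in between.

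At stake is a cost-saving figure that could be reported as the app's budget impact and taken up by hospitals, since the dissemination plan aims at open-access inpatient use after the study.

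**Working it through.** The protocol states no cost, budget-impact or utilisation figure, so there is nothing to reproduce. The check asks how large the window effect is when the app does nothing.

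**Inputs from the document**
- Windows of six months on each side, taken as 182 days.
- Before window ends at admission or baseline; after window starts at discharge.
- 100 patients with 20% dropout: 100 × (1 − 0.20) = 80 with follow-up.

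**Assumptions (not in the document)**
- d: days from admission to baseline, 0 to 28.
- r: true mean inpatient days per 182-day window, the same before and after (no app effect, no regression to the mean), 5 or 20.
- s: share of patients whose look-back ends at baseline, 50% or 100%.

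**Formula**
- Before window ending at baseline: d index-stay days plus r × (182 − d)/182 earlier days.
- After window: r days.
- Apparent saving per patient so anchored: d + r(1 − d/182) − r = d(1 − r/182).
- Averaged over all patients: s × d × (1 − r/182).

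**Results (days per patient)**

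| d | r = 5, all | r = 5, half | r = 20, all | r = 20, half |
|---|---|---|---|---|
| 0 | 0 | 0 | 0 | 0 |
| 3 | 2.92 | 1.46 | 2.67 | 1.34 |
| 7 | 6.81 | 3.40 | 6.23 | 3.12 |
| 14 | 13.62 | 6.81 | 12.46 | 6.23 |
| 28 | 27.23 | 13.62 | 24.92 | 12.46 |

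For example, d = 14 and r = 5 gives 14 × (1 − 5/182) = 13.62. The net figure is slightly below 14 because the index-stay days displace some earlier days from a window of fixed length. One extra stay, the index admission, is counted as well.

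**Check by simulation.** The set-up was 80 patients, 1,500 runs, no app effect, r = 5, 30% of patients with any inpatient days in a window, gamma-distributed days and exponential delays with mean 14. The mean apparent saving was 13.59 days with all patients anchored at baseline and 6.81 with half. With no delay it lay between −0.09 and 0.03 days over r = 5 and r = 10.

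**In money, as illustration only.** The document gives no unit cost. At an assumed 300 to 400 EUR per inpatient day, the 14-day case with all patients anchored at baseline runs from 12.46 × 300 = 3,738 EUR to 13.62 × 400 = 5,448 EUR per patient.

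**The comparison.** Anchoring at admission brings the window effect to zero but does not supply a without-app scenario. The app can be used only during the inpatient stay. With the look-back ending at admission, the index stay lies outside both windows; with the look-back ending at baseline, the days from baseline to discharge do. Either way, the named cost source does not cover the period of app use.

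**The case against.** The best defence is that the article gives the budget impact analysis a single sentence, and that scenarios and external inputs are normally set out in an analysis plan, which is not shown. That stands as far as silence goes. It does not cover what the article does state: two anchors treated as one, a t0 label that conflicts with the recruitment section, and a cost impact to be derived from costs that now come only from app patients.

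Several stronger readings are tempting, and the document does not support them:
- *That there are no costs without the app.* Pre-admission costs were incurred without it. What is missing is a comparable scenario; an external source is possible but none is named.
- *That index-stay days are always counted.* This needs the baseline anchor to be used, baseline to fall after admission, and no exclusion of index days. The text permits this but does not say it always applies.
- *That the analysis will subtract after from before.* The methods section does not say so. The Wilcoxon pre-post test is named for CGI, GAF and quality of life, not for costs.
- *That every bias favours the app.* Days in the index stay may displace outpatient contacts from the before window, which works the other way.
- *That the clinical pre-post tests will be read as app effects.* The sample size section says the focus is not on clinical effectiveness.

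The therapist reports in row 8 also soften the problem, since they are a second source for inpatient days. Row 8 names no anchor date, however, so it helps only together with the admission date.

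**Conclusion.** The point holds in a conditional form. The stated look-back can place index-stay days and the index admission in the before-costs and never in the after-costs. Its size depends on delay, prior utilisation and the share of patients anchored at baseline, none of which the document gives. For a 14-day delay with all so anchored, the net artefact is 12.5 to 13.6 inpatient days per patient. It halves if 50% are so anchored and vanishes if baseline is at admission. It becomes a false saving only if before and after are contrasted, which the named data invite but the text does not spell out.

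Independently of the window, the costs named for the budget impact analysis contain no comparable without-app scenario now that the control group is gone.

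This should be fixed, but it is not critical: the primary endpoint is recruitment and app use, which these data do not touch.

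**What to change.** 1. Delete the bracketed baseline alternative wherever it occurs in Table 2, row 6, and in the accompanying text, and end the look-back at the admission date for every patient.
2. Reconcile the t0 column label in Table 2 with the recruitment section, where t0 is study inclusion.
3. For patients already enrolled, remove days from admission to t0, and the index admission, using known admission dates and the therapist-reported treatment days in row 8. Where the question was asked from baseline, the corrected window covers only 182 − d days. The shortfall is r × d/182, which at d = 14 is 5 × 14/182 = 0.38 days or 20 × 14/182 = 1.54 days. State the days covered alongside the count.
4. Cost the index stay separately.
5. Report before-after costs as a descriptive course under inpatient care, not as the app's cost impact, unless a without-app source is named. Any utilisation effect in the budget impact analysis should be a labelled scenario.

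The cost is a change of questionnaire wording, a small recalculation for enrolled patients and a change of analysis wording. The study gives up an empirical cost-saving claim that its data cannot carry.

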### Oversight and monitoring

Access to the app is restricted to therapists (physician and psychologists) who were trained in its use. Detailed information material (“blended-ALMAMAR” manual) is provided by the study coordination center. Additionally, every clinic has appointed one responsible local coordinator. The local coordinators were trained ito be able to overview and supervise recruitment, data collection and adherence to the study protocol at the level of the single recruitment center. There is no independent Trial Steering Committee. The research team in the study coordination center reviews recruitment rates, data collection and data quality for all clinics on a regular basis and meets with all local coordinators of the clinics on a monthly basis to discuss key milestones as well as recruitment strategies. Regular monitoring visits will take place in every recruitment center, and a standardized procedure has therefore been developed. All data is coded directly into the database and all action are logged. Significant amendments to the original study protocol were provided to and approved by the responsible ethics committee.

